#### Secondary analyses

To account for PA at baseline, an analysis of covariance modelling approach will also be used (again including a random effect to account for clustering). These analyses will be repeated for the other outcome measures: time spent in sedentary behaviour, motor skills (measured by the TGMD-2)*,* anthropometrics (height, weight, body mass index, lean body mass, fat mass, percent body fat), physical environment (EPAO), and questionnaire data (attitudes, control beliefs, perceived competence, and intentions to increase PA). These analyses will be repeated for the same outcomes at the follow-up times. Predictive models for change in PA based on the questionnaire measures will also be developed. For all models, parameter estimates and 95% confidence intervals will be reported.

Specific to the cost analysis, the data of cost would include all the relevant costs of designing, implementing, monitoring, and analysing the RCT (labour/management cost, research cost, and capital cost). The cost effectiveness of the ABC intervention will be estimated using methods consistent with the guidelines established by the Panel on Cost-Effectiveness in Health and Medicine [80]. We will project costs as well as gains in both life-years and Quality-Adjusted Life Years (QALY) associated with the ABC intervention and with the no-intervention scenario. Health-related utility will be measured using the validated EuroQol five dimensions questionnaire (EQ-5D^TM^) index [81–83], which is a widely used questionnaire for calculating quality-adjusted life-years for assessing cost-effectiveness in healthcare.

Consistent with the panel’s recommendations, the societal perspective will be adopted, and future costs and benefits will be discounted to the present at an annual rate of 3%. The average relative performance of the ABC intervention will be assessed compared to no intervention, using a ratio of the additional expected cost of the program divided by the additional expected QALYs gained relative to the no-intervention alternative.

In addition to the intention-to-treat analyses, we will conduct per-protocol analyses including only preschool children from those daycare centres that were adherent. Evidence suggests that a compliance rate of about 60% is the threshold for achieving specified outcomes [73] and thus a conservative approach will be taken, defining adherence as those who reported complying to at least 70% of the intervention programming as measured by their log sheets.

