## Methods/design

### Study objectives

The primary objective of this study is to evaluate the efficacy of the ABC intervention program delivered in licensed daycare settings alone (intervention, daycare (DC)) vs. standard daycare curriculum (comparison (COM)) to increase preschoolers overall PA levels, specifically time spent in moderate to vigorous physical activity (MVPA).

The secondary objectives aim:

 To evaluate the potential additive contribution of a parent-driven home PA-promotion in addition to the daycare provider-facilitated intervention on its own (i.e., intervention DC vs. DC + HOME) To evaluate the efficacy of the ABC intervention arms to decrease the amount of time spent in sedentary behaviour To evaluate the effects of the ABC intervention arms on fundamental and gross motor skills in preschoolers attending daycare centres To evaluate the effects of the ABC intervention arms on preschool children’s anthropometrics, such as height, weight, body mass index, lean body mass, fat mass, and percent body fat To assess the effects of the ABC intervention on daycare providers’ attitudes, control beliefs, perceived competency, and intentions toward incorporating PA into the daycare curriculum, and examine whether these social-cognitive variables impact PA in children To evaluate the effects of the ABC intervention on child’s quality of life and on the quality of life of the parents as well To evaluate the costs of delivering the ABC intervention with the outcomes achieved to provide a valuable analytical framework to guide decision making by those who are responsible for allocating resources

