#### Questionnaires

In addition to a simple baseline demographics questionnaire, we will ask all parents about their child’s involvement in extra-curricular activities (sport, dance, music, art playgroups), and potential behaviour change at home (which will be validated by accelerometer data) so that we can account for participation in the analyses. We will collect information about the child’s health-related quality of life using the PedsQL^TM^ Measurement Model for the Pediatric Quality of Life Inventory instrument. The PedsQL^TM^ Measurement Model is a modular approach to measuring health-related quality of life from a multidimensional standpoint (physical, social, emotional, and school functioning) in children and adolescents. The tool is practical as it takes 4 minutes to complete and is reliable (internal consistency for the Total Scale Score: alpha = 0.88 Child Self-Report; alpha = 0.90 Parent Proxy-Report) [65].

The physical childcare environment will be rated using the relevant items from the validated Environment and Policy Assessment and Observation (EPAO) instrument. Construct and predictive validity of the physical activity environment domains, as well as inter-observer reliability of the EPAO instrument have been published previously [66–69]. The PA child behaviours portion of the EPAO instrument, created to evaluate a US-based healthy active living childcare program, is easily applied in the Canadian setting as it assesses the accessibility of the physical environment and facilities within the daycare setting that may promote or restrict PA.

Intervention daycare providers and parents will complete a questionnaire prior to the workshop/webinar training that assesses attitudes, control beliefs, perceived competence, and intentions, as well as support for increasing PA based on the Theory of Planned Behaviour [70, 71]. Following the workshop they will complete another that focuses on their understanding of the central health messages associated with ABC program.

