#### Cost analysis

A cost analysis will also be conducted to evaluate the costs of delivering the ABC intervention with the outcomes achieved to provide a valuable analytical framework to guide decision making by those who are responsible for allocating resources.

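### The cost data listed for the cost-effectiveness analysis are the costs of running the trial, which contradicts the program-cost numerator of the ratio and the objective of costing the delivery of ABC

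*Protocol article*

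**What the plan says.** Three places in the protocol article bear on what is to be costed.

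- **Purpose.** The last secondary objective under Study objectives reads "To evaluate the costs of delivering the ABC intervention with the outcomes achieved to provide a valuable analytical framework", meant to guide those who allocate resources. The Cost analysis section repeats the aim: "evaluate the costs of delivering the ABC intervention with the outcomes achieved".
- **Cost data.** Under Secondary analyses, the cost data are said to include "all the relevant costs of designing, implementing, monitoring, and analysing the RCT (labour/management cost, research cost, and capital cost"). The article gives no other list of cost inputs.
- **Ratio.** The same section compares ABC with a no-intervention scenario and gives the result as "a ratio of the additional expected cost of the program divided by the additional expected QALYs gained relative to the no-intervention alternative". It adopts a societal perspective and discounts at 3% a year.

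**The concern.** A cost-effectiveness ratio for a decision maker should carry the costs that follow from adopting the program. As described under the intervention headings, these are the provider workshops, manual and log sheets, music and guidebook, equipment kit and booster sessions and, in the home arm, the webinars, booklet and postcards. The listed cost data concern the trial instead, and research cost is named as a category of its own. An analyst who builds the numerator from the only itemised inputs would therefore include trial design, monitoring and analysis. The ratio would then overstate what a QALY costs under ABC, and the people it is meant to guide would see the program in too poor a light.

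**Working it through.** The article states no cost, utility, QALY or ratio, so there is no figure to reproduce. The check compares the texts and then works out the algebra.

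**Step 1: the listed items against the purpose.**

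| Listed item | Part of delivering ABC? |
|---|---|
| Designing the RCT | No |
| Implementing the RCT | In part: putting ABC into the centres is delivery, running the assessments is not |
| Monitoring the RCT | Not where it is trial monitoring |
| Analysing the RCT | No |
| Labour/management cost | Mixed |
| Research cost | No |
| Capital cost | Mixed |

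Reading the RCT as a slip for the program does not remove the conflict, because research cost would still be listed.

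**Step 2: effect on the ratio.** Let C be the incremental cost of delivering ABC, R the research cost charged to ABC, R0 the research cost charged to the comparator, and ΔQ the incremental QALYs. Take C > 0 and ΔQ > 0.

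- Ratio on delivery cost only: C / ΔQ
- Ratio with trial costs carried in: (C + R − R0) / ΔQ
- Multiplier: 1 + (R − R0) / C

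The stated comparator is the absence of intervention, a situation in which no trial is run. Then R0 = 0 and the multiplier is 1 + R/C. ΔQ cancels, so the factor does not depend on how utilities are obtained.

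**Step 3: illustrative values.** The values of R/C are assumptions, since the article supports none of them over another.

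| R/C (assumed) | Multiplier 1 + R/C |
|---|---|
| 0 (research costs left out) | 1 |
| 0.25 | 1.25 |
| 0.5 | 1.5 |
| 1 | 2 |
| 2 | 3 |
| 5 | 6 |

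With R0 = 0 the direction is fixed: any R above zero raises the cost per QALY.

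**The case against.** The strongest reply is that the sentence on cost data does not define the numerator. The ratio is defined a few lines later with program cost on top, and the objective and the Cost analysis section agree with it, so one sentence stands against three. This is right as far as it goes. A reader might infer that the plan puts trial costs in the numerator as a settled matter, and the text does not support that. What stands is the contradiction: the one place that itemises the inputs itemises the wrong ones.

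A second reply is that the ratio is incremental. Table 1 schedules most assessments alike in all three arms, so research costs shared equally would cancel (R = R0, multiplier 1). That holds if the analyst also charges research costs to the comparator. The article does not say so, and its comparator is a no-intervention scenario, which carries no trial cost.

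Two stronger readings are tempting and should be resisted.

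- **QALY data.** Because the Questionnaires section describes "health-related quality of life using the PedsQL" and does not name the EQ-5D, a reader might infer that the QALY denominator will have no data. The article does say "Health-related utility will be measured using the validated EuroQol five dimensions questionnaire" (EQ-5D), and Table 1 has a general row for quality-of-life questionnaires in all arms at baseline, 3 and 6 months. Who completes the EQ-5D and when is detail that a condensed article may leave to the full protocol.
- **Societal perspective.** A reader might infer that parents' time is excluded because no listed category names it. The list is not presented as closed, provider time can fall under labour, and the societal perspective is stated. This too is missing detail and not an error.

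**Conclusion.** The point holds as an internal contradiction. The listed cost data describe the trial, while the numerator and the stated purpose describe the program. If the list is followed, the cost per QALY is overstated by 1 + R/C. This assumes that the comparator bears no research cost and that both the delivery cost and the QALY gain are positive. If the numerator definition is followed instead, there is no distortion. The article gives neither R nor C, so no particular multiple can be claimed, and the values in the table show only how the factor behaves. The matter concerns a secondary objective and leaves the primary comparison untouched. It is still worth correcting, because the ratio is intended to inform decisions on resources.

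**What to change.** Rewrite the sentence on cost data so that it matches the ratio and the objective:

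- Limit the numerator to the incremental cost of delivering ABC: training, manuals, equipment and booster sessions, plus webinars and postcards in the home arm.
- Count provider and parent time, in keeping with the stated societal perspective.
- Exclude the costs of trial design, outcome assessment, trial monitoring and analysis, and report them separately as research costs.

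The cost of the change is the work of splitting the recorded costs into delivery and research. Mixed items, such as staff who both deliver booster sessions and collect data, need a stated rule for apportioning their time.

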In addition, each daycare centre in the intervention groups will be given the ABC resource training manual, recommended activity program outline with log sheets, music developed for PA with an outlined guidebook, and a starter kit of equipment that will form the basis of training for the daycare providers and the intervention itself. The manual is compiled with various ways providers can get children active in structured and unstructured physical activities, some of which target motor skill development. Our team will provide the educators with weekly schedules that suggest a set of activities, drawn from the ABC manual, that can be incorporated into the daily curriculum with the aim of meeting the Canadian Society for Exercise Physiology guidelines of accumulating at least 180 minutes of PA at any intensity spread throughout the day for preschool-aged children [37] and at least 60 minutes of MVPA for the children aged 5 years [53]. Additionally, these guidelines also suggest limiting the children’s sedentary time and minimizing screen time to less than 60 minutes a day for children aged 3 to 4 years, and limit recreational screen time to less than 2 hours for children aged 5 years [54]. These suggested activities have been broken down as locomotor skills, manipulative motor skills, and moving to music, shapes, and creative play. The program includes 60 minutes of structured activities, with the largest percentage (50%) of time spent on locomotor skills, as those are the higher intensity activities (such as running to play tag) and will more likely increase MVPA. Manipulative motor skill activities aid in developing gross motor skills which are important for major body movement such as walking, maintaining balance, coordination, jumping, and reaching. In addition to participating in PA, children with poor gross motor skills, may also have difficulty sitting in an alert position to watch classroom activity and writing on a blackboard. As a result, the second greatest percentage of time within the program is allocated toward gross motor development (33%) and 17% is devoted to creative play. On a daily basis, daycare providers will be asked to track facilitated physical activities using a simple pre-developed program tracking log sheet. Bi-monthly follow-up support or ‘booster’ sessions will also take place during regular hours within intervention daycare centres. These will be multi-dimensional, and include i) in-centre, ABC project staff-guided, structured PA sessions engaging both preschoolers and providers, ii) goal setting and iterative action planning regarding intervention delivery, and iii) performance monitoring and feedback related to implementation successes and, where relevant, overcoming barriers, troubleshooting, and problem solving.

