#### Comparison

Participating daycare centres that are randomized to the wait list control will continue to provide their regular curriculum during the study period. All comparison centres will be offered the ABC trial staff training and resources after the completion of data collection.

The primary outcome (MVPA) will be measured at baseline and at 3-months and 6 months post-intervention. The trial assessments and timeline are illustrated in Table 1. The baseline measurement will occur 2 weeks before the workshops to providers and parental webinars. This will include an assessment of PA and sedentary behaviour, body composition, fundamental and gross motor movement skills, and an assessment of the physical environment in daycare centres and homes as perceived by providers and parents, as well as attitudes, control beliefs, quality of life, perceived competency and intentions of providers and parents toward incorporating PA into the daycare curriculum and home environment, respectively. Immediately following the workshop and webinar training, attitudes, control beliefs, perceived competence, and intentions toward incorporating PA into the daycare setting and home environment will be measured. The parents receiving webinar training will be given an on-line ‘test’ to make sure they understood the training material. The components of the theory of planned behaviour, plus an assessment of any physical changes to the daycare or home environment (perceived by the provider or parent) will also be assessed at 6 months to determine the extent to which they predict PA at different time points. The 3-month evaluations will include children’s PA and sedentary behaviour, body composition and movement skills, as well as an evaluation of quality of life. The 6-month evaluation will include all of the 3-month measures and questionnaires, in addition to evaluations of the physical environment and theory of planned behaviour variables to examine associations with children’s PA.

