**Table 1 Tab1:** **Outcome assessments**

Activity Begins in Childhood (ABC)											
	Group 1: DC				Group 2: DC + HC				Group 3: COM		
	B	PW	3 mos.	6 mos.	B	PW	3 mos.	6 mos.	B	3 mos.	6 mos.
Consent Form	√				√				√		
Socio-Demographic Questionnaire	√				√				√		
Physical Activity Monitor Log	√		√	√	√		√	√	√	√	√
Environment Questionnaires					√		√	√			
EPAO	√		√	√	√		√	√	√	√	√
Gross Motor Assessment	√		√	√	√		√	√	√	√	√
Anthro Measures & Body Composition	√		√	√	√		√	√	√	√	√
Workshops/Webinar	√				√						
Workshop/Webinar Questionnaires	√	√		√	√	√		√			
Quality of Life Questionnaires	√		√	√	√		√	√	√	√	√
Pregnancy and Lifestyle Questionnaire	√				√				√		

B, baseline; mos, months; PW, post workshop; EPAO, Environment and policy assessment and observation.

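### The per-protocol rule selects centres on a self-reported log that only intervention centres keep, so it sets selected ABC centres against unselected controls and is not conservative about the effect

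*Protocol article*

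**What the plan says.** The last paragraph of *Secondary analyses* adds a per-protocol analysis to the intention-to-treat analyses: "we will conduct per-protocol analyses including only preschool children from those daycare centres that were adherent". The cut is justified by citing a lower threshold: "Evidence suggests that a compliance rate of about 60% is the threshold for achieving specified outcomes". From this the article infers its own stance: "thus a conservative approach will be taken". The rule that results is worded as "defining adherence as those who reported complying to at least 70% of the intervention programming as measured by their log sheets".

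The log sheets are described under *ABC intervention (common to DC and DC + HOME)*: "each daycare centre in the intervention groups will be given the ABC resource training manual, recommended activity program outline with log sheets". The staff who deliver the programme fill them in: "daycare providers will be asked to track facilitated physical activities using a simple pre-developed program tracking log sheet". Under *Comparison*, control centres "will continue to provide their regular curriculum during the study period" and are offered the ABC training and resources only after data collection. Table 1 does list a "Physical Activity Monitor Log" for all three arms, but that item accompanies the accelerometer and is not the programme log.

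*Primary analysis* fixes intention-to-treat for the DC versus COM comparison of MVPA at 6 months, using a mixed model with a random daycare effect. *Secondary analyses* introduces a baseline-adjusted version of that model.

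**The concern.** Adherence is observed after randomization, reported by the people being judged, and defined in the ABC arms only. Centres that log well may differ in staff motivation, or may already have had more active children. Dropping the poor loggers from one side only gives up the balance that randomization provided. Describing the cut as conservative invites a reader to treat the result as cautious.

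DC + HOME has a separate problem. The only adherence measure is a record of what providers did at the daycare. A centre could pass at 70% although its parents received little of the component that distinguishes the arm. DC versus DC + HOME is the first secondary objective, so a per-protocol version of that comparison would be hard to interpret.

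**Working it through.** **1. Who can be selected.** The definition refers to programme log sheets. DC and DC + HOME centres have them and COM centres do not. The rule can therefore screen ABC centres only, and all the selection falls on one side of DC versus COM.

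**2. What the 70% cut does.** Centres at or above 70% are a subset of those at or above 60%. Raising the cut keeps the same ABC centres or fewer, and drops those at 60–70% that the cited evidence would count as sufficiently compliant. This is stricter about adherence. It offers no protection against overstating the effect.

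**3. Which model applies.** The baseline-adjusted model appears earlier in *Secondary analyses*. The per-protocol paragraph names no model. The primary model's listed covariates are age, sex and organized extra-curricular activity, without baseline MVPA or season.

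**4. What the DC + HOME log covers.** It covers activities facilitated by providers. *Process evaluation* separately tracks parents' webinar attendance or online access and whether postcards were delivered on schedule. Neither enters the adherence definition.

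**5. Illustration of size.** The per-protocol rule has no figure of its own to reproduce, and no SD for MVPA is stated. From *Sample size*: 6 centres per group, 15 children per centre, ICC 0.08, difference 15 min/day, power 80%, two-sided 5%.

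- Design effect = 1 + 14 × 0.08 = 2.12. Effective n per arm = 90 / 2.12 = 42.5.
- Implied SD = 15 × √(42.45 / 2) / (1.960 + 0.842) = 24.7 min/day by normal approximation, or 22.2 using t with 10 df.
- The stated 6 per group fits an SD near 24 (41 × 2.12 = 87 children; 87 / 15 = 5.8, so 6 centres) but cannot be confirmed. An SD of 20 gives 4 centres and an SD of 30 gives 9.
- Between-centre SD = √0.08 × SD = 6.3 to 7.0 min/day.

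Suppose ABC has no effect, all 6 COM centres are kept, and only the k best-logging of 6 DC centres are kept. Let ρ be the correlation between log-sheet adherence and a centre's underlying MVPA. Expected spurious difference = ρ × (mean of the top k of 6 standard normal order statistics) × between-centre SD. SE ratio to 6 v 6 = √[(1/k + 1/6) / (2/6)].

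| DC centres kept | Mean of top k | Spurious difference, ρ = 0.3 to 1 (min/day) | SE ratio | Power for 15 min/day |
|---|---|---|---|---|
| 5 | 0.254 | 0.5 to 1.8 | 1.05 | 75–76% |
| 4 | 0.478 | 0.9 to 3.3 | 1.12 | 68–71% |
| 3 | 0.704 | 1.3 to 4.9 | 1.22 | 59–63% |

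At ρ = 0 the spurious difference is zero. For scale, the design SE by normal approximation is 15 / 2.80 = 5.4 min/day. The SD is back-solved, k and ρ are assumed, and the analysis is taken as unadjusted. Adjusting for baseline MVPA would remove part of the difference.

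**The case against.** Intention-to-treat is primary and the per-protocol analysis is only additional. Choosing adherent units after randomization is what every per-protocol analysis does. Detailed membership of analysis sets is often left to a fuller document, which is not shown here. All of this stands, and it limits the point to a supportive analysis. What remains is a rule that the article itself states and justifies, with a one-sided measure and a misleading label.

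A reader might infer that no comparator survives, because a COM centre cannot report 70% on a log it does not hold. That is too literal. Adherence is defined against intervention programming, and a COM centre's assigned condition is its usual curriculum, so keeping all COM centres is the natural reading. One sentence would settle it.

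A reader might also infer that the analysis is shown to favour ABC by a known amount. The document supports no such figure. The direction needs better-logging centres to be the more active ones. The *Discussion* makes that plausible by saying that centre policies and practices strongly affect children's activity, but it does not establish it.

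In defence of the wording, conservative can be read as describing the definition of adherence, and a margin above 60% is reasonable for self-reported logs. That supports keeping 70%. It does not support the word in a paragraph about an effect analysis.

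**Conclusion.** The concern holds in limited form. The per-protocol rule compares ABC centres selected on a self-reported post-randomization log with unselected controls. The paragraph does not tie it to the baseline-adjusted model. The stricter cut does not make the estimate conservative. The DC + HOME definition omits the component that defines the arm.

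The bias cannot be sized from the document. It is probably towards ABC, and nil if logging is unrelated to centre MVPA. The range of 0.5 to 4.9 min/day, against a 15 min/day target, is illustrative only: it rests on a back-solved SD of 22.2 to 24.7, on 3 to 5 of 6 DC centres being kept, and on ρ between 0.3 and 1. The primary conclusion is not affected.

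It may seem that a complier-average effect should replace the analysis. That estimator assumes that assignment does nothing in centres below 70%, yet those centres still receive workshops, manual, music, equipment and staff-led boosters. With 4 of 6 centres adherent it would divide the whole intention-to-treat effect by 4/6, a 1.5-fold inflation, and so could itself overstate ABC.

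**What to change.** Amend the per-protocol paragraph as follows.

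- State that all COM centres are retained and that the adherence rule applies to the ABC arms.
- Fit the model with baseline MVPA and season as covariates and a random centre effect. Baseline MVPA is already collected and season is a stratification factor.
- Label the result non-randomized and supportive to intention-to-treat.
- Delete the word conservative. Keep 70% as the cut and show 60% as a sensitivity.
- For DC + HOME, add parental webinar access and postcard delivery, both already tracked in the process evaluation, to the adherence definition. Because *Home environment* lets parents take hard copies instead of webinars, say how those parents count.

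Do not substitute a complier-average effect.

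No new data collection is needed. The cost is slightly more analysis work, possibly fewer DC + HOME centres classed as adherent, and some loss of between-centre degrees of freedom to the season term, which matters with so few centres.
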